### 3.1.1. Stage 1 – Preliminary safety and feasibility study

In Stage 1, the feasibility, safety and tolerability of point-of-care G6PD testing and PQ7 in G6PD normal (>70%) patients will be determined in 4 selected health facilities with staff undertaking clinical review on day 3 and also day 7 to ensure patient safety. Stage 2 will only proceed after review of the Stage 1 data by SRT and SMC.

After 3 months, the revised case management will be rolled out at 4 selected sites (2 in Indonesia and 2 in PNG), initiating Stage 1. The remaining sites will continue the Pre-Implementation Stage. Stage 1 is anticipated to last 6 months, during which a total of 800 patients with *P. vivax* malaria (~500 from Indonesia and ~300 from PNG) will be treated (Figure 1).

All patients that are eligible for and consent to participate in the study, will be tested by quantitative G6PD activity assessment using the G6PD STANDARD (SD biosensor, ROK). Patients with G6PD activity >70% ( $\geq 6.1$  U/gHb) will be prescribed primaquine at a total dose of 7 mg/kg over 7 days (PQ7) and those with 30-70% activity (4.1-6.0 U/gHb) will be prescribed the same total dose of primaquine over 14 days (PQ14). Patients with G6PD activity <30% ( $\leq 4.0$  U/gHb) will be prescribed primaquine at a dose of 0.75 mg/kg/week for 8 weeks (PQ8w).

The safety review team (SRT) will review all AESI (adverse event of special interest) and SAE (severe adverse event) data after every 100 patients treated with primaquine and may request to review additional data if there are safety concerns. A formal interim analysis is planned after enrolment of 400 patients (~150 patients from PNG, ~250 patient from Indonesia). The SRT will review the interim analysis outputs and share with the Safety Monitoring Committee (SMC) who will conduct an interim review and issue a recommendation regarding continuation of Stage 1.

At the end of Stage 1, once 800 patients (~300 patients from PNG, ~500 patients from Indonesia) have been enrolled, a final analysis will be conducted and reviewed by the SRT and presented to the Safety Monitoring Committee. We anticipate that 700 patients will have been treated with PQ7 and 100 with PQ14. Prior to study start the SMC will be tasked with defining specific *a priori* criteria that will be used to decide whether the study progresses directly to the main feasibility study for wider roll out in Stage 2 without changes in the protocol, whether the implementation package needs to be revised or if the study needs to be discontinued. The final analysis of Stage 1 will be reviewed by the SRT and summarized to support the SMC final review. If the SMC recommends progression to Stage 2, the data

summary, together with the SMC recommendations will be shared with the NDoH and NDA for approval to progress to Stage 2.

### 3.1.2. Stage 2 – Large-scale implementation and feasibility study

Stage 2 of the study will be a feasibility study conducted at 10 community health-care facilities: 6 sites in Indonesia and 4 sites in Papua New Guinea. The primary purpose of Stage 2 is to determine the feasibility and cost-effectiveness of the complete revised case management initially studied in Stage 1. Robust Pre-Implementation malarimetric surveillance for a minimum of 12 months along with quantitative surveys of baseline operational metrics and costs will be followed by coordinated introduction of the revised case management across all study health facilities and a minimum of a further 12 months of surveillance – creating an interrupted time series comparing the endpoints listed in section 2.2.2.

During Stage 2 study procedures will be the same as those for Stage 1, except that the procedures will be performed by routine healthcare staff. All patients will be reviewed by community health workers (CHW) at home 3 days after starting PQ. The review may also take place at the health facility, if the patient presents there. Exceptionally, the follow-up may also take place via a phone call if the patient is not physically reachable at home. The CHW will complete a signs and symptom checklist to detect early indicators of haemolysis or other AESI. Patients with signs of haemolysis or other AESI will have their primaquine ceased and will be referred to the health facility for medical review. Patients tolerating their medication will be encouraged to adhere to a full (7 or 14 days) course of treatment. Safety outcomes occurring between day 3 and end of treatment will be detected passively by community-based health workers, study health facilities and regional hospitals.

Continuous surveillance and pharmacovigilance over the entire study period will enable interrupted time-series analyses of malarimetric indices (see section 2.2.2).

Figure 1 presents the study schedule for the baseline data, pre-implementation stage, and stages 1 and 2.

**Figure 1. Study overview**[figure not shown]

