| S1.SE6 | Proportion of patients who were reviewed on day 3 and day 7.                                                                                                                                                                                                                                                |

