- G6PD deficient (<30% enzyme activity). Should not receive daily primaquine.

S2.SE5 Proportion of vivax malaria patients that are reviewed on day 3.

S2.SE6 Proportion of vivax malaria patients that adhere to their prescribed primaquine regimen defined as follows:

- The proportion of patients who self-report that they have taken all prescribed PQ doses between the time of the initial prescription and the follow-up visit.

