### 3.2 Inclusion and exclusion criteria

**Inclusion criteria Stage 1 of the study (and thus receipt of either PQ7, PQ14 or PQ8w) are:** age >1 year (PNG) or ≥6 months (Indonesia), haemoglobin concentration ≥8 g/dl and signed agreement of patient or their carers to participate in the study and comply with all study-specific obligations, including attending follow-up clinical evaluations (at day 3 and day 7). Inclusion criteria for Stage 2 will be the same except that patients will only need to be able to attend a follow-up appointment (or receive a phone call) on day 3.

**Exclusion criteria:** pregnant and lactating females with infants <6 months in Indonesia and <1 year in PNG and patients with severe manifestations of malaria will not be prescribed primaquine and will not be enrolled in Stage 1. These patients will contribute incidence data to Stage 2 of the study but will not receive primaquine treatment. Patients' ineligible for primaquine treatment will be treated according to current national guidelines.

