| daily dose <
0.25mg/kg                                                                  |  |  |  |  |  |  |  |  |  |  |  |
| PQ8W n(%)                                                                           |  |  |  |  |  |  |  |  |  |  |  |
| daily dose >
1.25mg/kg                                                                  |  |  |  |  |  |  |  |  |  |  |  |
| daily dose <
0.38mg/kg                                                                  |  |  |  |  |  |  |  |  |  |  |  |
|                                                                                            |  |  |  |  |  |  |  |  |  |  |  |
| FOLLOW UP
DEVIATIONS                                                            |  |  |  |  |  |  |  |  |  |  |  |
| Proportion of
Patients without
Day3 Review (Day
3-5) N(% of all
enrolled pts)  |  |  |  |  |  |  |  |  |  |  |  |
| Proportion of
Patients without
Day7 Review (Day
6-10) N(% of all
enrolled pts) |  |  |  |  |  |  |  |  |  |  |  |

**Table S2. Baseline characteristics of individuals presenting to health facilities by pre-implementation and post-implementation (Stage 2) phases of study for each health facility site**

*Example table give for 2 health facility sites from PNG*

|                                      | PNG health
facility site 1 |                                      | PNG health
facility site 2 |                                      |
|--------------------------------------|---------------------------------------|--------------------------------------|---------------------------------------|--------------------------------------|
|                                      | Pre-
implementation                | Post-
implementation
(Stage 2) | Pre-
implementation                | Post-
implementation
(Stage 2) |
| Number of
individuals     | N                                     | N                                    | N                                     | N                                    |
| Number of
individuals per | x (x, x) [min, max]                   | x (x, x) [min, max]                  | x (x, x) [min, max]                   | x (x, x) [min, max]                  |

|                                    |  |  |  |  |
|------------------------------------|--|--|--|--|
| health facility site        |  |  |  |  |
| Age, years (mean and range) |  |  |  |  |

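### Table S1a counts a missing day 7 review as a Stage 2 follow-up deviation, although the Stage 2 text and endpoints schedule only a day 3 review

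*SAP*

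**What the plan says.** For Stage 1, section 3.1.1 has "staff undertaking clinical review on day 3 and also day 7 to ensure patient safety", and S1.SE6 in section 2.2.1 is the "Proportion of patients who were reviewed on day 3 and day 7".

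For Stage 2, section 3.1.2 opens its description of procedures with "During Stage 2 study procedures will be the same as those for Stage 1, except that the procedures will be performed by routine healthcare staff". It then gives the detail: "All patients will be reviewed by community health workers (CHW) at home 3 days after starting PQ", with review at the facility or by telephone as alternatives. After that, "Safety outcomes occurring between day 3 and end of treatment will be detected passively by community-based health workers", the study facilities and regional hospitals. Section 3.2 keeps the Stage 1 inclusion criteria except that "patients will only need to be able to attend a follow-up appointment (or receive a phone call) on day 3". S2.SE5 in section 2.2.2 is the "Proportion of vivax malaria patients that are reviewed on day 3", and the review component of S2.PE1 is the community review on day 3.

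Appendix 3 has two deviation tables. Table S1 is for Stage 1. Table S1a is titled for Stage 2, has ten facility columns, and was added for Stage 2 in version 7.0 according to the revision history. Under follow-up deviations, both have one row for patients without a day 3 review (days 3 to 5) and one for patients without a "Day7 Review (Day 6-10"), each as a percentage of all enrolled patients.

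**The concern.** A table shell tells the programmer what to count. Table S1a defines the event (no day 7 review), the window (days 6 to 10) and the denominator (all enrolled Stage 2 patients). Nothing in the table marks the row as not applicable, and no footnote gives it a Stage 2 meaning.

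If the row is filled in as written, patients managed exactly as sections 3.1.2 and 3.2 describe are listed as deviating from the protocol. What is at stake is the credibility of the Stage 2 deviation report. Readers of a feasibility study will look to that table to see how well follow-up was delivered. A large count for a visit that the text does not schedule would sit next to the count that does matter, patients without a day 3 review, and could draw attention away from it.

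**Working it through.** The plan states no figure for this row, so there is nothing to reproduce. The check is a comparison of the places that bear on Stage 2 review, followed by simple arithmetic to size the consequence.

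**Step 1. Places that fix the Stage 2 review**

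| Place in the SAP | Review in Stage 2 |
|---|---|
| Section 2.2.2, S2.PE1 | Day 3 |
| Section 2.2.2, S2.SE5 | Day 3 |
| Section 3.1.2, detailed sentences | Day 3, then passive detection to end of treatment |
| Section 3.2 | Day 3, by visit or phone call |
| Section 3.1.2, opening sentence on procedures | As in Stage 1, apart from who performs them |
| Appendix 3, Table S1a | Day 3 and day 7, each missing review a deviation |

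The first four agree. The fifth would by itself carry over the Stage 1 day 7 review, but the sentences after it narrow it to day 3. The sixth cannot be squared with the first four.

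**Step 2. Where the row comes from**

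The two follow-up rows of Table S1a are those of Table S1. In Stage 1 both are right, because day 3 and day 7 are both scheduled and S1.SE6 measures both. In Stage 2 only the day 3 row has a counterpart in the text (S2.SE5).

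**Step 3. Size, if the day-3-only schedule is what is carried out**

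Inputs:
- N = 11,410, the predicted Stage 2 enrolment (section 4.2.1).
- u = share of patients who happen to have a review on days 6 to 10. The SAP does not give it, so it is an assumption.

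Count in the day 7 row = N × (1 − u).

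| Assumed u | Calculation | Count | Share |
|---|---|---|---|
| 0% | 11,410 × 1.00 | 11,410 | 100% |
| 1% | 11,410 × 0.99 | about 11,296 | 99% |
| 5% | 11,410 × 0.95 | about 10,840 | 95% |
| 10% | 11,410 × 0.90 | 10,269 | 90% |
| 20% | 11,410 × 0.80 | 9,128 | 80% |

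With the row removed, the day 7 count is zero by construction and only the day 3 row remains.

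**Step 4. Reach**

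S2.PE1 and S2.SE5 have no day 7 component. Section 6.2 analyses all enrolled patients and excludes nobody for a deviation. The methods in section 9 do not draw on Table S1a. The effect stops at the deviation table.

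**The case against.** The strongest defence is that the SAP, read as a whole, leaves little doubt about the Stage 2 schedule. The opening sentence in section 3.1.2 is a general lead-in, the sentences after it give the day 3 detail, section 3.2 contrasts the two stages explicitly, and the endpoints draw the same line. Table S1a is a dummy table that repeats the Stage 1 rows. The day 7 row is separate and labelled, so it cannot contaminate the day 3 count.

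Much of this stands. A reader might infer from the opening sentence that the SAP sets two competing Stage 2 schedules. The text does not support that: the sentence is loose because it omits one difference, and its own continuation resolves it. A reader might also infer that the row undermines the answer to the primary feasibility question. It does not, because S2.PE1 asks only for the day 3 community review.

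The defence does not dispose of Table S1a itself. The table was added specifically for Stage 2, so it is not a Stage 1 shell used by oversight for both stages. Its being a dummy table is no answer either, since the purpose of a shell is to fix what the output will count.

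**Conclusion.** The point holds as a reporting error in Table S1a. The Stage 2 deviation table counts the absence of a day 7 review, while the Stage 2 text and endpoints schedule only day 3.

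Its size rests on two assumptions: that the day-3-only schedule is what is carried out, and that the row is filled in as written. Then every patient without an incidental contact on days 6 to 10 is listed as a deviation, which is 80% to 100% of patients if 0% to 20% have such a contact. It is tempting to state that nearly every one of the 11,410 patients would be a false deviation. The documents do not support that as a fact, because they give no share of patients with day 6 to 10 contacts.

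The reported Stage 2 follow-up deviations would be misstated. S2.PE1, S2.SE5 and the analysis sets are unaffected. The point is worth correcting before the table is programmed, but no effect estimate depends on it. Nothing here says which review schedule is clinically right.

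**What to change.** Reconcile Table S1a with S2.SE5 and sections 3.1.2 and 3.2.

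- If the day-3-only schedule stands, remove the day 7 row from Table S1a. In section 3.1.2, name the absence of a day 7 review as a second difference from Stage 1, next to the change of staff.
- If a day 7 review is in force in Stage 2, S2.SE5 and sections 3.1.2 and 3.2 must say so, and the row can stay.

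The first option costs one table row and one clause in the SAP. The second costs wording in three places. Neither needs new data or a change to any analysis method.

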### 3.2 Inclusion and exclusion criteria

**Inclusion criteria Stage 1 of the study (and thus receipt of either PQ7, PQ14 or PQ8w) are:** age >1 year (PNG) or ≥6 months (Indonesia), haemoglobin concentration ≥8 g/dl and signed agreement of patient or their carers to participate in the study and comply with all study-specific obligations, including attending follow-up clinical evaluations (at day 3 and day 7). Inclusion criteria for Stage 2 will be the same except that patients will only need to be able to attend a follow-up appointment (or receive a phone call) on day 3.

**Exclusion criteria:** pregnant and lactating females with infants <6 months in Indonesia and <1 year in PNG and patients with severe manifestations of malaria will not be prescribed primaquine and will not be enrolled in Stage 1. These patients will contribute incidence data to Stage 2 of the study but will not receive primaquine treatment. Patients' ineligible for primaquine treatment will be treated according to current national guidelines.

## 4 Sample size

### 4.1 Stage 1

In the Stage 1 preliminary study of the feasibility and safety of the implementation package, 4 health facilities will enrol 800 patients (~500 in Indonesia and ~300 in Papua New Guinea). Assuming 764 of these patients will have a G6PD activity >70% and be eligible for PQ7, and that the proportion of patients receiving short-course primaquine who have to stop therapy within 7 days is 5%, this sample size will produce a 95% confidence interval for the true proportion needing to stop treatment of +/- 1.55%.

### 4.2 Stage 2

**NOTE:** *Given slower than expected recruitment in Stage 1, the predicted patient recruitment in Stage 2 was revised down on 5 August 2024 to 70% of eligible patients (n=11,410) across Indonesia and Papua New Guinea. Additionally, an error was detected in the original power calculation for detection of a reduction in incidence of vivax malaria. In protocol vs 5.0, the total number of patients with vivax malaria recruited into the study was erroneously predicted to be 16,300 over 18 months (the initial timeframe for the study) when in reality this was the number of patients predicted over 12 months. This resulted in an underestimate of the monthly case incidence at each clinic and thus an underestimate of the power available for detection of an incidence reduction.*

*The revised and corrected power and precision calculations are provided below with the original erroneous calculations retained for reference. Power calculations for detection of an individual-level reduction in risk of vivax malaria recurrence are also provided.*

#### 4.2.1 Revised and corrected Stage 2 power and precision calculations

Assumptions underlying the following Stage 2 power calculations include the following:

1. 5% of patients are ineligible for the intervention package (pregnancy, lactation, severe malaria, age <6m (Indonesia) or <1 yr (PNG)).
2. The impact on the risk and rate of infection will be the same across different endemic sites.
3. The mean baseline risk of *P. vivax* recurrence at 6 months is 20%
4. Loss to follow-up in both groups is 10%
5. Alpha = 0.05

During the 12-month pre-implementation period, a total of **17,160** patients with *P. vivax* (mono or mixed infections) presented to the ten study clinics (see Table 1). Assuming 5% of patients are ineligible for enrolment due to pregnancy, lactation or age under 6 months (Indonesia) or 12 months (PNG), this gives an estimated maximum number of patients eligible for recruitment into Stage 2 of **16,300**.

**Table 1 Number of patients with vivax malaria attending the ten study clinics in last 12 months**

| Clinic name     | Country   | Locality               | Estimated total number of P. vivax episodes per year | Estimated maximum recruitment in SCOPE Stage 2 (95%) |
|-----------------|-----------|------------------------|-------------------------------------------------------------|------------------------------------------------------|
| Timika          | Indonesia | Timika, Southern Papua | 3173                                                        | 3014                                                 |
| Bhintuka        | Indonesia | Timika, Southern Papua | 1164                                                        | 1106                                                 |
| Pasar Sentral   | Indonesia | Timika, Southern Papua | 4937                                                        | 4690                                                 |
| Wania           | Indonesia | Timika, Southern Papua | 3681                                                        | 3497                                                 |
| Tanjung Leidong | Indonesia | North Sumatra          | 500                                                         | 475                                                  |
| Hanura          | Indonesia | Lampung                | 450                                                         | 428                                                  |
| Baro            | PNG       | West Sepik             | 417                                                         | 396                                                  |
| Mugil           | PNG       | Madang                 | 1044                                                        | 992                                                  |
| Napapar         | PNG       | East New Britain       | 412                                                         | 391                                                  |
| Wirui           | PNG       | East Sepik             | 1382                                                        | 1313                                                 |
| Total           |           |                        | 17,160                                                      | 16,302                                               |

Footnotes: Estimates based on previous clinic records and number of patients with *P. vivax* recruited over last 12 months. Maximum enrolment assumes 5% of patients are ineligible because they are pregnant, lactating or under 6-12 months of age.

## **S2.SE15 - Incidence Rate Reduction**

The proportion of patients recruited into SCOPE has been lower than expected and this will impact on the predicted reduction in incidence. The revised estimated reduction in incidence and predicted power to show this are provided in Table 2, with varying levels of recruitment (0.5-1).

**Table 2 – Power to detect a reduction in the incidence of *P. vivax* malaria**

| Proportion of eligible P. vivax malaria patients recruited | Eligible patients over 12 months period | Predicted mean monthly incidence at each clinic preintervention | Predicted absolute incidence reduction | Predicted mean monthly incidence at each clinic post intervention | Power to detect predicted incidence reduction |
|-------------------------------------------------------------------|-----------------------------------------|-----------------------------------------------------------------|----------------------------------------|-------------------------------------------------------------------|-----------------------------------------------|
| 1                                                                 | 16,300                                  | 135.8                                                           | 24.44                                  | 111.36                                                            | 99.5%                                         |
| 0.9                                                               | 14,670                                  | 135.8                                                           | 22.00                                  | 113.80                                                            | 98.4%                                         |
| 0.8                                                               | 13,040                                  | 135.8                                                           | 19.56                                  | 116.24                                                            | 95.5%                                         |
| 0.7                                                               | 11,410                                  | 135.8                                                           | 17.11                                  | 118.69                                                            | 89.3%                                         |
| 0.6                                                               | 9,780                                   | 135.8                                                           | 14.67                                  | 121.13                                                            | 78.6%                                         |
| 0.5                                                               | 8,150                                   | 135.8                                                           | 12.22                                  | 123.58                                                            | 63.2%                                         |

**Example STATA code:** power pairedm 135.8 111.36, sddiff(15) n(10) alpha(0.05).

Based on previous estimates, 60% of cases of *P. vivax* malaria seen at each clinic are due to relapse and therefore preventable with improved radical cure. We predict the intervention package will reduce the individual risk of relapse by 30%. With anticipated recruitment of 70% of eligible patients, the total predicted sample size in Stage 2 would fall to **11,410** patients receiving primaquine over 12 months of enrolment. Based on this lower predicted enrolment and using the assumptions as above, the predicted absolute reduction in incidence at each clinic would be 17.11 cases per month  $((135.8 \times 0.6) \times 0.3 \times 0.7)$  and resultant power to detect this difference would be **89.3%**.

